#### Heart/pulse rate variability analysis

2.2.6

The autonomic nervous system constantly regulates sBP and heart rate and the oscillations at different frequencies in these signals therefore reflect the status of the ANS regulation. We will extract metrics in both time domain and frequency domain. In the time domain, we will compute RMSSD between inter-beat intervals of sinus beats.

There are several reasons that we select RMSSD as the primary measure: (1) RMSSD is particularly sensitive to short-term, high-frequency variations in heart rate, making it an excellent index for capturing rapid vagal modulation of heart rate (42). (2) RMSSD demonstrates superior mathematical properties compared to pNN50, including better statistical stability when analyzing short segments of data (43). (3) RMSSD is less affected by respiratory rate changes compared to other time-domain measures, which is particularly important in mechanically ventilated TBI patients (44).

In the frequency domain, as highlighted in (45) and (42), the LF component (0.04–0.15 Hz) was previously known as the baroreceptor range, as it primarily reflects baroreceptor activity under resting conditions. LF power can be influenced by both the parasympathetic and sympathetic nervous systems, as well as by blood pressure regulation through baroreceptors. The sympathetic nervous system generally does not produce rhythms above 0.1 Hz, whereas the parasympathetic system can influence heart rhythms down to 0.05 Hz, which corresponds to a 20-s rhythm. Under resting conditions, the LF band is indicative of baroreflex activity rather than cardiac sympathetic innervation. During periods of slow breathing, vagal activity can induce oscillations within the LF band. The HF component (0.15–0.4 Hz) is closely tied to respiratory rates, which is why it is also referred to as the respiratory band. The rate of breathing modulates vagal activity through respiratory sinus arrhythmia, the natural increase and decrease in heart rate that occurs with inhalation and exhalation. Hence, the HF band is predominantly a measure of parasympathetic influence on the heart. Because observed RR interval samples are non-uniformly spaced in time, we will use the well-established Lomb-Scargle power spectral density (PSD) estimator to calculate PSDs of the RR interval sequence (46). From the calculated PSD of the RR interval sequence, we will derive the LF/HF ratio.

For the case of eAD characterization utilizing ABP signal alone, we will extract pulse-to-pulse interval (PPI) based on detected systolic blood pressure from high-quality ABP waveforms and calculate pulse rate variability. We identify the intervals between fiducial points in successive pulses as PPI. Based on PPI time series, we will calculate RMSSD, the ratio of LF/HF and BRS metrics in place of using RR interval time series.

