However, in the severe traumatic brain injury (sTBI) population, the interpretation of frequency-domain HRV metrics is complicated by several factors. Mechanical ventilation, often required for sTBI patients, can artificially alter respiratory patterns, impacting HF power and respiratory-related heart rate modulation. Additionally, the use of sedation and analgesic medications, common in sTBI management, can directly affect autonomic regulation and HRV patterns. Intracranial pressure fluctuations, characteristic of sTBI, can independently influence autonomic regulation and cardiovascular variability. Furthermore, hemodynamic management strategies involving vasopressors and fluid management can affect blood pressure variability and consequent autonomic responses. Baguley et al. investigated dysautonomia following sTBI based on the HRV analysis, finding significant differences in HRV among TBI patients, controls, and between dysautonomia and non-dysautonomia subjects (17). Froese et al. assessed the physiological relationship between pressure reactivity index (PRx) and HRV, BP, and baroreflex sensitivity (BRS) using time-series statistical methodologies in sTBI patients. They demonstrated a stronger connection between BRS, HRV, and PRx, indicating sympathetic autonomic response related to cerebrovascular reactivity derangements (18). Therefore, while these frequency-domain metrics provide valuable insights into autonomic regulation, their interpretation in sTBI patients should account for these confounding factors and be integrated with other autonomic assessment measures for a more comprehensive evaluation of autonomic dysfunction.

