### Recruitment

2.1

We will collect data from an ongoing multi-center randomized controlled trial examining the efficacy of a sTBI treatment strategy guided by both ICP and brain tissue oxygen (PbtO2) as compared to a strategy guided by ICP monitoring alone [Brain Oxygen Optimization in sTBI (BOOST), Phase 3, NCT03754114] (17). As part of the trial, the ECG waveform with four-leads and arterial blood pressure waveform data will be collected over the first 5 days of their intensive care unit (ICU) stay. Our ancillary study (AUTO-BOOST) will leverage this rich and granular waveform data to fully characterize autonomic dysfunction following sTBI.

We are sourcing data from this active clinical trial (BOOST), the trial has enrolled 550 patients. Since unexpected issues may arise during data collection, such as failures to collect data due to leads detaching or errors caused by device malfunctions, we estimate that approximately 50% of patients will have adequate cardiac telemetry data of sufficient quality for analysis. The Moberg monitor (CNS Monitor, Moberg ICU Solutions, Amber, Pennsylvania, United States) will capture and time-synchronize these analog data with other vital signs, ventilator data, and ICP/PbtO2 data, storing all data locally. A research team member will extract and upload the waveform data to a secure IBM cloud-based server. We will extract ABP, ECG data, and ventilator parameters from the Moberg device, deriving heart rate from the raw ECG tracing. We will use cleaned segments of stable recordings within 24 h of ICU admission for analysis.

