## Statistical analysis

3

The characterization of eAD requires consideration of age-specific analysis. We will stratify patients into age to account for known age-related differences in autonomic function; Within each age stratum, we will establish reference distributions based on published normative data for that specific age group; For each autonomic measure, we will use age-appropriate reference ranges from healthy controls as reported in large-scale studies. Normally, RMSSD values should fall between 19 and 75 ms (48), HRT should exhibit a turbulence onset near 0% and a turbulence slope above 2.5 ms/R-R interval (49), and BRS is around 4.87–34.07 across different age groups over 20 years old (50).

For the determination of eAD, we will quantify the incidence and magnitude of anomalies such as reduced RMSSD, HRT, and BRS, alongside increased low frequency (LF) power and an elevated LF/HF ratio, which are critical indicators. eAD will be characterized if three or more of these indicators exceed or fall below 2.5 standard deviations from age and sex-standardized values. Autonomic function measures will also be considered as continuous variables as well. For the primary analysis, we will use data from patients over their first 24 h following ICU admission to identify eAD, as well as examine the association of these measures with clinical outcomes. In exploratory analysis, we will describe autonomic function measures over the first 5 days following ICU admission.

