When interpreting autonomic indices, particularly LF/HF ratio, several important caveats must be considered. The traditional interpretation of LF/HF as a simple marker of sympathovagal balance is problematic in acute TBI patients for several reasons. First, respiratory rate, which significantly influences HF power, is often mechanically controlled in these patients. Second, medications commonly used in TBI management, such as beta-blockers and vasopressors, directly affect autonomic modulation. Third, altered intracranial pressure and cerebral autoregulation can independently influence cardiovascular variability. Therefore, we recommend interpreting LF/HF alongside other autonomic measures and within the context of each patient’s clinical status, medication profile, and ventilatory parameters. This multi-parameter approach provides a more reliable assessment of autonomic dysfunction than relying on any single metric alone.

There are still some limitations in this study. Currently, this study incorporates both linear (time and frequency domain) and non-linear (PRSA) approaches to analyze autonomic function. The inclusion of PRSA as a non-linear method is particularly valuable as it can capture complex patterns of cardiovascular regulation that may be missed by traditional linear analyses. Future studies might benefit from incorporating additional non-linear methods such as entropy measures and detrended fluctuation analysis to provide an even more comprehensive assessment of autonomic dysfunction in severe TBI. Another limitation of our study is the inability to fully control for numerous confounding factors that can influence autonomic function in the critical care setting. While we account for age through stratification and statistical adjustment, several other important confounders remain uncontrolled. These include pharmacological interventions (such as vasopressors, analgesics, sedatives, beta-blockers, and anti-edema medications like mannitol), mechanical ventilation parameters, arterial CO2 levels, and timing of various therapeutic interventions. Future studies should consider implementing more complex statistical methods to better account for these factors.

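### LF power and LF/HF are computed in fixed bands whatever the breathing rate, so two of the five eAD indicators can shift with the ventilator setting

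*Protocol article*

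**What the plan says.** All references are to the protocol article.

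- **Bands.** Section 2.2.6 (Heart/pulse rate variability analysis) says of LF that "the LF component (0.04–0.15 Hz) was previously known as the baroreceptor range" and of HF: "The HF component (0.15–0.4 Hz) is closely tied to respiratory rates, which is why it is also referred to as the respiratory band". Section 1.2 gives the same limits. The index follows directly: "From the calculated PSD of the RR interval sequence, we will derive the LF/HF ratio". No step links the bands to the patient's breathing rate.
- **Slow breathing.** Section 2.2.6 itself notes: "During periods of slow breathing, vagal activity can induce oscillations within the LF band".
- **Ventilation.** Section 1.2 says: "Mechanical ventilation, often required for sTBI patients, can artificially alter respiratory patterns, impacting HF power and respiratory-related heart rate modulation". The Discussion adds: "First, respiratory rate, which significantly influences HF power, is often mechanically controlled in these patients". It advises reading LF/HF alongside ventilatory settings and lists ventilation among the confounders left uncontrolled.
- **Data in hand.** Section 2.1 (Recruitment) says: "We will extract ABP, ECG data, and ventilator parameters from the Moberg device, deriving heart rate from the raw ECG tracing".
- **Counting rule.** Section 3 (Statistical analysis) names reduced RMSSD, HRT and BRS, "alongside increased low frequency (LF) power and an elevated LF/HF ratio, which are critical indicators", and calls eAD when at least three lie beyond 2.5 SD of age- and sex-standardised values. Section 4 (Expected results) uses the same 3-of-5 rule over 24 h, but takes lower LF power and a lower LF/HF as the abnormal direction.

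**The concern.** HF power represents respiratory (vagal) modulation only while the breathing frequency lies inside the HF band. If a ventilator sets a rate outside it, the spectral indices change although autonomic modulation has not. The reference values come from healthy controls and are standardised for age and sex, so standardisation cannot absorb a machine-set rate.

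The advice to interpret LF/HF in context has no place to act, because a threshold is counted and not interpreted. The error would sit in the eAD label itself. Adjusting an outcome model for ventilation would correct neither a patient's label nor the reported incidence of eAD.

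**Working it through.** The article gives no figure on this point to reproduce. The check converts the bands, works out which index moves and in which direction, and illustrates the size on assumed inputs.

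**1. Band limits in breaths per minute (Hz × 60).** LF: 0.04 × 60 = 2.4 to 0.15 × 60 = 9. HF: 0.15 × 60 = 9 to 0.40 × 60 = 24.

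**2. Which index moves.**
- Below 9/min (and above 2.4/min): respiratory power passes from HF to LF. LF rises, HF falls, LF/HF rises.
- Above 24/min: respiratory power lies beyond 0.40 Hz. HF falls and LF/HF rises; LF power is unchanged.

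**3. Size, by simulation.** Every input here is an assumption: 1-h RR series analysed in 5-min windows by Lomb-Scargle, heart rate 80/min, a 15 ms oscillation at 0.09 Hz, a respiratory oscillation of 15 ms (range 5–30 ms), noise SD 5 ms. Results are multiples of the value at 14 breaths/min, with the range over 5–30 ms in brackets.

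| Rate | LF power | HF power | LF/HF |
|---|---|---|---|
| 8/min | ×1.95 (1.11 to 4.90) | ×0.08 (0.43 to 0.03) | ×23 (2.6 to 168) |
| 26/min | ×1.03 (1.00 to 1.03) | ×0.08 (0.43 to 0.03) | ×12 (2.3 to 39) |

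At 10–20/min all three stay within about 8% of the reference. Exactly on the edges there is partial leakage: LF/HF ×1.28 to ×3.67 at 9/min and ×1.25 to ×1.59 at 24/min.

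A hand check of LF at 8/min: a sinusoid of amplitude A has power A²/2, so the 15 ms LF oscillation carries 112.5 ms². Adding the respiratory power gives (112.5 + 12.5)/112.5 = 1.11 for 5 ms, (112.5 + 112.5)/112.5 = 2.0 for 15 ms, and (112.5 + 450)/112.5 = 5.0 for 30 ms. This agrees with the simulation.

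**4. Direction of the error.** Under section 3 (high LF and high LF/HF abnormal) the shift pushes towards a false indicator: two indicators below 9/min, one above 24/min. Under section 4 (low values abnormal) the same shift moves away from the abnormal side and can mask an indicator.

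**5. Effect on the 3-of-5 rule, section 3 direction.** Suppose the distorted indicators do cross 2.5 SD, and the others are independent, each abnormal with probability q. Then P(eAD) is P(X ≥ 3) with 5 indicators if none is forced, P(X ≥ 2) with 4 if one is forced, and P(X ≥ 1) = 1 − (1 − q)³ if two are forced.

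| q (assumed) | None forced | One forced | Two forced |
|---|---|---|---|
| 0.0062 (one-sided 2.5 SD tail) | 0.000002 | 0.0002 | 0.019 |
| 0.20 | 0.058 | 0.18 | 0.49 |

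For example, 1 − 0.8³ = 0.488.

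**The case against.** The strongest reply is that the problem is disclosed. The article describes the effect of ventilation on HF, calls the usual reading of LF/HF problematic in these patients, and chooses RMSSD as its primary measure partly because of ventilation. Segment-level handling of ventilator data may also sit in a fuller plan that is not shown. This stands in part: the authors know of the confounding. But the counting rule is stated, and as stated it does not carry out their own caveat, although ventilator data are extracted.

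A reader might infer more than the documents support:

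- **That any rate outside 9–24/min distorts both spectral indicators.** LF power has its own band and is affected only below 9/min.
- **That a false indicator is created.** This needs the section 3 direction and a shift beyond 2.5 SD. Section 4 reverses the direction, and no SD for LF power or LF/HF and no ventilator rates are given.
- **That the ventilator alone can produce eAD.** One or two forced indicators do not reach three.
- **That a fixed fold-change applies to every affected hour.** The multiples follow from chosen amplitudes and noise. Moreover, eAD is defined on values over 24 h, and no rule says how hourly values combine.

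A further objection concerns the remedy. Section 2.2 computes HRT only with more than 10 PVCs in the hour and excludes it for ABP-only data. Without HRT, four indices remain. Removing LF/HF leaves three, and removing LF power as well leaves two, which can never meet the rule. Simple exclusion would then turn possible false positives into built-in negatives. This objection stands, and the fix has to deal with it.

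**Conclusion.** The point holds in a limited form. The bands are fixed, the 9 and 24 breaths/min limits follow from them, and the eAD rule uses LF power and LF/HF without regard to respiratory rate. The label can therefore depend on the ventilator setting, through both indices below 9/min and through LF/HF alone above 24/min. Whether the error creates or hides an indicator cannot be settled until sections 3 and 4 are reconciled.

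The simulated LF/HF multiples show that the shift can be large, but they rest wholly on assumed inputs. The frequency of affected hours, the crossing of 2.5 SD and the effect on the 24-h label are not shown by the documents. The change is worth making because it is cheap and confined to the analysis.

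**What to change.** 1. Reconcile sections 3 and 4 on the direction in which LF power and LF/HF count as abnormal.
2. From the extracted ventilator data, flag each 1-h segment with a respiratory rate outside 9–24/min. State how the rate within an hour is summarised and how rates on the limits are handled. This assumes that respiratory rate is among the extracted ventilator parameters, which the article does not list.
3. When forming the 24-h value, treat LF/HF from flagged segments as not evaluable, and LF power too when the rate is below 9/min. Do not treat them as normal.
4. Report the hours and patients affected and the number of evaluable indices per patient. Do not classify a patient with fewer than three evaluable indices as eAD-negative.
5. Add two sensitivity analyses of eAD: HF centred on the recorded rate, and the fixed bands in all hours.

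The cost is analysis-plan wording and the use of data already extracted. The downside is fewer evaluable spectral indices in some patients, mainly where HRT is unavailable or only ABP is recorded. Nothing here bears on how patients are ventilated.

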We will assess ABP signal quality using a singular value decomposition (SVD)-based approach (24). We will use our previously developed pulse detection algorithm to mark the onset of each ABP pulse, normalizing each pulse in both time and amplitude (25). Once the onsets of pulses are identified, we will adjust each pulse to a fixed length using spline resampling to ensure consistency in the number of data points across all pulses. Additionally, we will standardize each pulse’s amplitude by centering it around zero and scaling it to a standard deviation of one. Then, we will project this ABP pulse onto the signal subspace based on the SVD approach and calculate the signal-to-noise ratio. To obtain the signal and noise subspaces, we will implement SVD approach on an expert-validated reference library of 567 ABP pulses collected from 51 patients hospitalized at UCLA Ronald Reagan medical center. These valid ABP pulses will be subjected to the same normalization process. We will define the signal subspace and noise subspace after conducting SVD valid ABP pulses in the reference library. For a test ABP pulse, we will first project it onto the signal subspace and calculate the ratio of the energy of the projected signal over that of the projected noise. This ratio will be compared with a threshold, which is defined as the minimum calculated ratio among all the 567 pulses in the reference ABP library. This setting ensures that any ABP pulse closely resembling any pulse in the validated library is assessed correctly, providing a robust measure against false detections. The valid ABP pulses are those with calculated ratio greater than the threshold. We will conduct subsequent analysis only on the one-hour segments that pass both ECG and ABP signal quality assessments.

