#### Peaks detection

2.2.2

We will recognize R peaks for each ECG beat using a published QRS detection algorithm that includes four steps (26). The first step will use a sliding window of 2 s to capture the ECG signal. In the second step, we apply a band-pass filter ranging from 0.5 to 17 Hz to eliminate signal noise and motion artifacts. Then, we apply an enhancement mask to the filtered signal as Equation 4:

(4)
$$S\left(n\right)=\overset{k}{\underset{j=-k}{\sum }}M\left(k+j\right)E\left(n+j\right)$$

The enhancement mask 
M
 is defined as Equation 5:

(5)
$$\left\{\begin{array}{c} M\left(n\right)=-1,n\in \left[0,k-1\right]\\ M\left(n\right)=2*k,n=k\\ M\left(n\right)=-1,n\in \left[k+1,2k\right] \end{array}\right.$$

where 
E
 is the filtered ECG signal and 
S
 is the enhanced ECG signal. To eliminate variations in QRS amplitude, we will normalize the amplitude of the enhanced ECG signal to 1 using min-max normalization.

The third step is the detection of QRS fiducial points based on detected crests and troughs. Based on the normal range of the QRS complex in a typical lead-II ECG waveform, as shown in a published work, we will use a searching range of 0.3 s to detect the QRS complex. The searching process starts at the first point of the normalized ECG signal, and the amplitude threshold for detecting the QRS complex will be defined as 0.5 mV (26). The last step is the R peak recognition based on the detected QRS fiducial point. Since a normal QRS rangs is less than 0.12 s, the time interval for recognizing R peak is set as 0.24 s centering at the fiducial point in (26), and we identify the R peak successively.

For the high-quality ABP waveform, we will detect systolic blood pressure based on a published algorithm (27). Initially, we will apply a Savitzky–Golay filter to remove noise. Subsequently, we will utilize a sliding window to correctly identify the maximum point of the arterial pulse.

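### In ABP-only patients, pulse-interval RMSSD, LF/HF and BRS face the one set of reference values and eAD rule given for RR intervals with no agreement check, so timing error of unstated size can mask a reduced RMSSD

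*Protocol article*

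**What the plan says.** All places are in the protocol article.

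- **Interval source (2.2.6).** In the ABP-only case, "we will extract pulse-to-pulse interval (PPI) based on detected systolic blood pressure from high-quality ABP waveforms and calculate pulse rate variability". The next sentence is less specific: "We identify the intervals between fiducial points in successive pulses as PPI". The fiducial is therefore tied to the systolic point but not otherwise named.
- **How the systolic point is found (2.2.2).** After a Savitzky–Golay filter, "we will utilize a sliding window to correctly identify the maximum point of the arterial pulse".
- **What is computed (2.2.6).** From the pulse intervals, "we will calculate RMSSD, the ratio of LF/HF and BRS metrics in place of using RR interval time series".
- **Another timing point already exists (2.2.1).** For the ABP quality step: "We will use our previously developed pulse detection algorithm to mark the onset of each ABP pulse". It is not mentioned for pulse intervals.
- **Reference values (3).** Healthy-control ranges are used. For RMSSD the only one quoted is "RMSSD values should fall between 19 and 75 ms", with no separate range for pulse intervals.
- **eAD rule (3 and 4).** Three or more indices must lie beyond 2.5 SD of age- and sex-standardized values. Section 4 counts five indices: RMSSD, HRT, BRS, LF power and LF/HF.
- **ABP-only group (2.2 and 5).** HRT is dropped because PVCs are hard to detect without ECG. eAD is then examined in the groups with and without ECG, and no different definition is given.

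**The concern.** RMSSD, which section 2.2.6 selects as the primary measure, is built from differences between successive intervals. Each interval is itself a difference between two beat times. Error in locating a beat therefore enters several times and inflates RMSSD. The relative inflation is largest when true beat-to-beat variability is small, and that is the state the study wants to detect.

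The plan substitutes pulse intervals for RR intervals one for one, and the only reference values and eAD rule it gives are those used for RR intervals. Nothing described would show how far the two series disagree. At stake is eAD classification in the ABP-only group, where one of the five indices is already missing and each remaining index carries more weight.

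**Working it through.** The article states no timing error, no ABP sampling rate and no cut-off in milliseconds, so there is no figure of its own to reproduce. The steps below show how the result depends on the unknowns.

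**1. Error model.** Let beat i be timed at t(i) + e(i), with independent errors of SD s. The successive interval difference gains e(i+2) − 2e(i+1) + e(i), whose variance is (1 + 4 + 1)s² = 6s². With the Appendix definition of RMSSD,

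RMSSD_obs = sqrt(RMSSD_true² + 6s²).

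The added term is never negative.

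**2. Observed RMSSD by assumed s.**

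| s (ms) | true 5 ms | true 10 ms |
|---|---|---|
| 2 | 7.0 | sqrt(100 + 24) = 11.1 |
| 4 | 11.0 | sqrt(100 + 96) = 14.0 |
| 6 | 15.5 | sqrt(100 + 216) = 17.8 |

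Sampling alone, without interpolation, gives s = step/√12. At an assumed 125 Hz this is 8/√12 = 2.3 ms, and a true 10 ms reads 11.5 ms. At an assumed 250 Hz it is 1.2 ms, and the reading is 10.4 ms.

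**3. The relevant cut-off.** The rule is 2.5 SD, not the quoted lower limit of 19 ms. Assume that 19–75 ms is a 95% range:

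- Normal: mean 47, SD = 56/(2 × 1.96) = 14.3, cut-off 47 − 2.5 × 14.3 = 11.3 ms.
- Lognormal: log-mean 3.631, log-SD 0.350, cut-off exp(3.631 − 2.5 × 0.350) = 15.7 ms.

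The jitter that lifts a true value to cut-off c is s = sqrt((c² − RMSSD_true²)/6):

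- from 10 ms: 2.1 ms (normal) or 5.0 ms (lognormal);
- from 5 ms: 4.1 ms or 6.1 ms.

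The answer depends on how the range is read. If 19–75 ms were mean ± 1 SD, the normal cut-off would be 47 − 2.5 × 28 = −23 ms, and no RMSSD could count as reduced. The lognormal cut-off would be 6.8 ms: a true 10 ms would not be abnormal at all, and a true 5 ms would be masked at s = 1.9 ms.

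**4. Effect on LF/HF.** In a simulated series of 4,500 beats with true RMSSD 6.3 ms and LF/HF 4.0, jitter of 4 ms gave 11.7 ms and 3.0, and jitter of 8 ms gave 20.4 ms and 1.8. Jitter lowers LF/HF. Section 3 counts an elevated ratio as abnormal and section 4 a decreased one, so the same shift would hide an abnormality under the first and imitate one under the second.

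**5. Effect on the three-index rule.** Without HRT, section 2.2.6 names three indices from pulse intervals: RMSSD, LF/HF and BRS. If only these are used, all three must be abnormal, and a masked RMSSD removes eAD. If LF power is also taken from pulse intervals, a masked RMSSD removes eAD only when exactly three of the four are abnormal and RMSSD is one of them.

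**The case against.** - **The size is unknown.** No timing error or sampling rate is given, and filtering and pulse screening come first. This stands, and every magnitude above is conditional. The screening is not a clear safeguard, however: it rescales each pulse to a fixed length and amplitude and judges its shape, and nothing in it tests beat-to-beat peak timing.
- **19 ms is not the decision limit.** A reader might infer that jitter must carry RMSSD to 19 ms, or that reaching it defines normal for eAD. The documents do not support that. From a true 10 ms it would take s = 6.6 ms, whereas the rule works at 2.5 SD. Under the 95% reading that cut-off is lower and needs less jitter.
- **Hidden eAD is not a certain result.** A reader might infer that eAD is bound to be under-called in ABP-only patients. Sections 3 and 4 disagree on the abnormal direction of LF/HF, and it is not stated whether LF power is used here. The net effect on eAD cannot be signed.
- **Pulse onset is not shown to be better.** A reader might infer that onset timing would cure the problem. Nothing in the article shows that it is more precise than the systolic peak.
- **Pooling is not planned.** Section 5 examines eAD within each subgroup and states no combined analysis or formal comparison, and section 3 also treats the measures as continuous. This limits the consequence, but misclassification within the ABP-only group remains.
- **The article is condensed.** Pulse-specific references could sit in a fuller plan. That is possible. The article nevertheless states the one-for-one substitution outright, beside a single set of ranges and a single rule.

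**Conclusion.** The point holds in a limited form. The plan puts systolic-peak pulse intervals in place of RR intervals and gives one set of reference values and one eAD rule, with no agreement check described. Independent timing error biases RMSSD upward only, so from this source a reduced RMSSD can be missed but not invented. The bias is 6s² on the squared scale, with s unknown. Under the assumption that 19–75 ms is a 95% range, roughly 2–5 ms of jitter would carry a true 10 ms past the cut-off.

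This rests on errors that are independent from beat to beat and unrelated to the true intervals, and on the assumed reading of the reference range. A masked RMSSD decides eAD if only RMSSD, LF/HF and BRS are used. The effect through LF/HF stays open until sections 3 and 4 are reconciled, and the effect on BRS was not quantified. The documents do not establish that eAD will be hidden in this subgroup, only that the plan as described could not tell.

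**What to change.** 1. In the one-hour segments that pass both ECG and ABP quality assessment (section 2.2.1), also run the ABP-only pipeline. Report paired pulse-minus-RR differences for RMSSD, LF/HF and BRS.
2. In the same hours, time pulse intervals from both the systolic peak and the pulse onset already marked in section 2.2.1. Use whichever agrees better with RR, and name it in section 2.2.6.
3. Use the paired differences to calibrate the ABP-only values or cut-offs before classifying eAD in ABP-only patients.
4. State which indices enter the eAD rule when HRT is unavailable, and reconcile the direction of LF/HF between sections 3 and 4.

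The cost is some extra analysis of recordings and detections that already exist, with no new data collection. The drawback is that calibration uncertainty carries into ABP-only eAD and should be reported with it. If the paired differences prove negligible, little has been lost and the substitution is supported by evidence.
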